Fitness professionals will follow the 2008 PA guidelines safety recommendations for PA programming tailored to persons with CKD and will be trained on communication skills and behavioral techniques (goal-setting, action planning, self-monitoring, provide instruction, feedback on performance, opportunities for social comparison, peer modeling, and social support) [45]. Two sessions/week will be offered, slowly progressing towards 50 min of light-to-moderate PA per session. Persons will also be encouraged to accumulate additional minutes of moderate PA throughout the week, primarily through increased walking for leisure and transportation. Interventions are structured around “*Move and Learn*” formats. They will include health education, led PA and lifestyle behavior change segments modeled after evidence-based sources (interventions examples are shown in Table 3) [46]. The social dynamics of the group will be used to forge strong, sustainable relationships with participants and reach appropriate minutes per week of PA, collect data using Health IT resources and provide guidance at the end of 8-week core intervention for transitioning to maintenance and self-managed PA. We will continue to offer the intervention even if the the participant initiates dialysis. For particiapnts who recently underwent surgery for dialysis access, we will encourage participation but limit arm exercise.

**Table 3 Tab3:** Study Procedures and measurements

	Baseline	Follow-up: 1	Follow-up: 2
		8 weeks	16 weeks
Self-reported			
Physical activity vital sign	√		
Medical history (or any changes thereof)	√	√	√
Quality of life (SF-12)	√	√	√
Qualitative Interview^a^	√		
Adverse events		√^b^	√
MEASUREMENTS			
Grip strength	√	√	√
6-min walk test	√	√	√
Anthropometry (measured BMI, waist circumference)	√	√	√
Blood pressure and blood glucose level	√	√	√
Weekly physical activity as measured by Garmin PA monitor	√	√^b^	√
INTERVENTIONS			
Brief physical activity counseling	√		
Wearable physical activity monitor	√	√	√
Group exercise sessions		√	

^a^in a subset of patients recruited at start of study

^b^assessed continually during the study in G2

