### Primary outcome

#### Minutes per week of physical activity

The Study main outcome will be assessed objectively using the Garmin vivofit werable device. Weekly minutes of moderate-to-vigorous PA will be synchronized every week using the Quantextual application. In case of problems we will also manually sync the werable devices at the V1 and V2 measurement time points. In addition, weekly number of steps, sleep hours and minutes of sedentary time will also be collected.

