### Quality assurance and trial coordination

We will implement a clear set of quality assurance steps for trial coordination and delivery of the intervention. Pre-specified recruitment criteria and protocols, rigorous training of personnel at both sites, and monitoring of sites with feedback will help assure high-quality study findings. In order to deliver the multi-level PA intervention strategy uniformly across sites, we will conduct training and certification, provide standardized tools, conduct site-initiation visits, team meetings, and study staff role into each existing patient flow. Data will be collected using standardized tools and instruments. All safety concerns, acute events [e.g., myocardial infarction injuries], or mortality noted during 16-weeks of trial follow-up will be compared between study arms and reported to oversight committees.

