#### Potential risks

Adverse effects of exercise: Minor risks include muscle soreness, light-headedness/dizziness, and weakness. Physical activity may lead to more serious health problems such as a heart attack and sudden death. However, this is very rare. Estimates of sudden cardiac death range from 0 to 2 per 100,000 h of physical activity. Physical Activity may also lead to acute spikes in blood pressure and/or blood glucose if the patient is not well-controlled. Group exercise classes will be led by trained professionals who are able to offer suggestions to limit and prevent these adverse events. Session will also include measurements of blood pressure and glucose to identify potential contra-indications for exercise that day. Fitness professionals will be trained to recognize medical emergencies and seek emergency care if needed. A potential participant’s nephrologist will be informed of their patient’s possible participation in our trial and if they determine a patient is medically unfit to participate, they will be excluded from the study.

Participants will be informed at each visit and exercise session that if at any point during the study they develop chest pain, shortness of breath, lightheadedness, or fall they should stop activity immediately and inform study staff if currently at a study visit or call 911 if at home. In the event of milder symptoms at home, they are advised to call study coordinators to inform them of their symptoms as they may alter future intervention. Participants’ nephrologist will be notified of all events and reported symptoms and will review the case before study should be continues.

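### Adverse events are assessed continually in group 2 only, yet safety is compared between arms, so minor events will tend to look more frequent in group 2

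*Protocol article*

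**What the plan says.** Table 3 of the protocol article (Study Procedures and measurements) ticks adverse events at 8 and 16 weeks. The 8-week tick carries footnote b: "assessed continually during the study in G2". No section provides continual adverse-event assessment for group 1.

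Under Quality assurance and trial coordination, safety concerns, acute events and deaths "noted during 16-weeks of trial follow-up will be compared between study arms" and reported to oversight committees.

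Two other sections bear on how events come to light:

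- **Group-based physical activity program.** For group 2, "Two sessions/week will be offered" within an 8-week core period.
- **Potential risks.** Sessions include blood pressure and glucose measurement. The instruction on warning symptoms is repeated at visits and sessions: "Participants will be informed at each visit and exercise session that if at any point during the study they develop chest pain". For milder symptoms at home, participants in either arm have a telephone route: "they are advised to call study coordinators to inform them of their symptoms".

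Footnote b also sits on the 8-week tick of the Garmin activity row. The text on the wearable gives the device to all participants, and the primary outcome section says: "Weekly minutes of moderate-to-vigorous PA will be synchronized every week using the Quantextual application". Neither is limited to one arm.

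**The concern.** A between-arm comparison of adverse events is interpretable only if events have the same chance of being recorded in each arm. Here the plan fixes a more intensive ascertainment rule for one arm and then compares the arms. The events most exposed are those that depend on being noticed or mentioned: soreness, dizziness, minor falls, and blood pressure or glucose excursions. They are also among the effects of exercise most likely to be seen in this trial.

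An apparent excess in group 2 could then come from closer observation alone. That would count against the referral programme that the trial hopes to disseminate. Analysis cannot fully repair it later, because group 1 events that were never recorded cannot be recovered.

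**Working it through.** The article states no figure on this point, so there is nothing to reproduce. The check is a reading of the sections together, a count of contacts and an illustration.

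**1. Ascertainment by arm**

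| | Group 1 | Group 2 |
|---|---|---|
| Scheduled adverse-event collection (Table 3) | Weeks 8 and 16 | Weeks 8 and 16, plus continual assessment |
| Staffed sessions with blood pressure and glucose measurement | None | Two per week in the core period |
| Instruction on warning symptoms | At visits | At visits and sessions |
| Spontaneous telephone report | Yes | Yes |

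**2. Scheduled post-baseline contacts at which an event can come to light**

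- Group 2: 2 sessions/week × 8 weeks = up to 16 sessions; 16 + 2 visits = up to 18.
- Group 1: 2 visits.

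**3. Apparent risk ratio at equal true risk**

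Let p be the true risk in both arms, and c1 and c2 the proportions of affected participants recorded in groups 1 and 2. The observed ratio is (p × c2)/(p × c1) = c2/c1. The article gives no capture proportions. Assume c2 = 1:

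- c1 = 0.90: 1/0.90 = 1.11
- c1 = 0.70: 1/0.70 = 1.43
- c1 = 0.50: 1/0.50 = 2.00

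With equal capture the ratio is 1.00.

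**4. Chance of a false signal**

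The sample-size section gives 98 participants with 50% per arm, so 98 × 0.5 = 49. The true risks of 20% and 40%, and the choice of a two-sided Fisher test at 0.05, are assumptions. Exact binomial enumeration gives the probability of a significant excess in group 2:

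| Group 1 capture | True risk 20% | True risk 40% |
|---|---|---|
| 100% | 1.4% | 1.5% |
| 90% | 2.5% | 3.9% |
| 70% | 7.3% | 17.7% |
| 50% | 18.8% | 50.3% |

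The direction follows from the design. The size follows only from the assumed capture and risk.

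**5. The Garmin row**

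Table 3 limits continual assessment to group 2 on the 8-week tick. The text gives every participant the device, with weekly syncing and a manual sync at both follow-up visits if there are problems. The 16-week tick carries no footnote, and 16 weeks is the time point of the primary comparison under Expected outcome. The table and text disagree, but unequal capture of the primary outcome does not follow.

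**The case against.** The strongest reply is that group 1 is not unobserved. All participants are told to report serious symptoms and to telephone about milder ones, and nephrologists are notified of what is reported. This stands: it would be wrong to say that group 1 events are captured only by recall at two visits. But an open telephone line is spontaneous reporting and does not match continual assessment with regular staff contact.

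A reader might also infer that group 2 is questioned about adverse events at every session. The article does not say so. It describes instructions and measurements at sessions and, separately, continual assessment. The gap in intensity is stated; its exact form is not.

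Third, the examples given for the safety comparison include infarction and death, which would probably surface in either arm. That limits the concern to lesser events. However, the comparison is worded to cover all safety concerns, so the lesser events are in it.

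Fourth, safety is not among the listed primary or secondary outcomes and is not powered, and closer watching of the arm doing supervised exercise is understandable. The likely bias overstates harm in group 2 rather than hiding it. All of this lowers the stakes. None of it makes the planned comparison fair, and closer watching can continue alongside a common schedule.

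Finally, a reader might infer from the Garmin row that group 1 has device data only at visits, so that the primary outcome is measured unequally. The operative text contradicts that reading, and the footnote is absent from the 16-week tick. Only an inconsistency remains.

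**Conclusion.** The point holds for adverse events. As written, ascertainment is more intensive in group 2 and the arms are then compared, so minor and self-reported events will tend to appear more frequent in group 2 at equal true risk. Deaths and infarctions are probably little affected.

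The article does not allow the bias to be sized. The ratios of 1.11 to 2.00 restate assumed capture of 90% to 50% in group 1 against full capture in group 2, and should be read only as an illustration. The false-signal probabilities rest further on the assumed true risks, the assumed test and 49 per arm.

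For the device, the conclusion is narrower: footnote b and the text must be reconciled. The article does not show that primary-outcome capture differs by arm.

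**What to change.** - Solicit adverse events in both arms with the same question on the same schedule, for example a short prompt in the smartphone app that both arms already receive, plus the 8- and 16-week visits. Reword footnote b on the adverse-event row to match.
- Base the between-arm safety comparison only on events found by this common method. List events detected at exercise sessions separately, as a description of group 2.
- Correct footnote b on the Garmin row so that it agrees with the text, which already describes weekly syncing without limit by arm.
- Recruitment has begun at one site. Identify participants followed before the change when safety is reported, since their group 1 events were collected under the sparser schedule.

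The cost is a table correction, an app prompt and a small burden on participants. Lack of internet access is already an exclusion, so the prompt should be feasible in both arms. Safety monitoring at the sessions need not change.

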## Measurements

Table 2 displays the data that we will collect during the study data. We plan to collect study data using Research Electronic Data Capture (REDCap) electronic data capture tools hosted at Emory University and Stanford University. REDCap is a secure, web-based application designed to support data capture for research studies providing 1) an intuitive interface for validated data entry; 2) audit trails for tracking data manipulation and export procedures; 3) automated export procedures for seamless data downloads to common statistical packages; and 4) procedures for importing data from external sources.

### Primary outcome

#### Minutes per week of physical activity

The Study main outcome will be assessed objectively using the Garmin vivofit werable device. Weekly minutes of moderate-to-vigorous PA will be synchronized every week using the Quantextual application. In case of problems we will also manually sync the werable devices at the V1 and V2 measurement time points. In addition, weekly number of steps, sleep hours and minutes of sedentary time will also be collected.

### Secondary outomes

#### Questionnaires

The Center for Epidemiological Studies-Depression questionnaire (CES-D): CES-D20, is a 20-item instrument that asks individuals to rate how often over the past week they experienced symptoms associated with depression, such as restless sleep, poor appetite, and feeling lonely. Response options range from 0 to 3 for each item (0 = rarely, 1 = little of the time, 2 = much of the time, 3 = almost all the time). Scores range from 0 to 60, with high scores indicating greater depressive symptoms. The CES-D also provides cutoff scores (e.g., 16 or greater) that aid in identifying individuals at risk for clinical depression, with good sensitivity and specificity and high internal consistency [47]Short Form Health Survey (SF-12) [48]. The SF-12 questionnaire consists of 12 questions to measure functional health and wellbeing of the including a global question of perceived health status, to which the respondents indicate whether they think their overall health is excellent, very good, good, fair and poor. It covers the same eight health domains as the SF-36 with one or two questions per domain. The maximal number of points is 100 which in turn represents the best possible health condition and quality of life. SF-12 have been validated among dialysis patients and is in strong agreement with those derived from SF-36 in this population (*r* = 0.94 for both physical and mental component) [49].McAuley physical activity self-efficacy questionnaire [50]: The Exercise Self-Efficacy Scale assesses an individual’s beliefs in their ability to continue exercising on a three time per week basis at moderate intensities for 40+ minutes per session in the future. For each item, participants indicate their confidence to execute the behavior on a 100-point percentage scale comprised of 10-point increments, ranging from 0% (not at all confident) to 100% (highly confident). Total strength for each measure of self-efficacy is then calculated by summing the confidence ratings and dividing by the total number of items in the scale, resulting in a maximum possible efficacy score of 100.

#### 6-min walk test

All eligible participants will undergo 6-min walk test according to American Thoracic Society’s guideline [51]. In short, the test will be performed indoors on a 30 m straight course. Participants graded their dyspnea and fatigue perception on the 10-scale Borg scale. At the end of the 6-min period the distance, heart rate and blood pressure will be measured, and immediate fatigue and dyspnea scores will have reassessed. The participants will receive the same instructions before the walk and will be encouraged by the investigator who will repeat the set of phrases every 30s during the walk.

#### Grip strength

We will carry out an assessment of grip strength in a standardized manner i.e., in neutral position of arm, forearm, and wrist. We will measure three consecutive attempts (with one-minute intervals in between) with a digital dynamometer (Takei 5401; Takei Scientific Instruments, Inc). All measurements will be done on setting II as suggested by Firrell and Crain and recorded in kilograms [52] . The same dynamometer will be employed for all participants. Calibration will be done automatically (electronic zero calibration system). For each participant, the arithmetic mean value of 3 measurements with the dynamometer will be used for statistical analysis. This method shows high repeatability [53].

## Statistical analysis

### Sample size justification

The study is powered on between-arm differences in the proportion achieving the primary outcome, minutes per week of moderate-level PA. Our sample size estimation is guided by PA counseling and referral review studies report an effect size between 0.09 and 0.71 for achieving PA guidelines [54–58]. We used the formula given in Vierron and Giraudeau [59] and Vittinghoff and Fitzmaurice [60] with an adjustment for the intraclass correlation coefficient (ICC), where N is the total sample size, the Z’s are the critical value for type I (α = .05) and type II (β = .2) error, σ^2 is the variance in outcome, ρ is the ICC, and π is the proportion (50%) of the N persons assigned to the treatment group. Based on the above formula, assuming an ICC of 0.5 [61], our total sample size of 98 will provide 89% power to detect a 100 min/week of moderate PA difference between groups, corresponding to an effect size of 0.46. Considering an estimated 30% loss to long-term follow-up as reported in similar exercise intervention trials [62], our plan to enroll 98 participants should provide adequate power (80%) to detect differences across intervention arms. Data gathered from those who withdraw from the study will not be used for statistical analyses. This has been accounted for when completing the power analysis, with an additional 20% added to the target sample size. Attrition may be for a number of reasons, which will be ascertained upon withdrawal where possible.

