**Methods/design:**

We describe a pragmatic clinical trial for an exercise intervention among patients transitioning to dialysis. We will use an existing framework – Exercise is Medicine (EIM) – developed by the American College of Sports Medicine. After undertaking formative qualitative research to tailor the EIM framework to the advanced CKD population (eGFR < 30 ml/min/1.73m^2^), we will randomize 96 patients from two regions—Atlanta and Bay Area—in two intervention arms with incremental levels of clinical-community integration: physical activity assessment during Nephrology clinical visit, brief counseling at pre-dialysis education, and physical activity wearable (group 1) versus group 1 intervention components plus a referral to a free, EIM practitioner-led group exercise program over 16 weeks (group 2; 8 week core intervention; 8-week follow up). We will assess efficacy by comparing between group differences in minutes/week of objectively measured moderate intensity physical activity. To evaluate implementation, we will use questionnaires for assessing barriers to referral, participation and retention along the path of the intervention. Further we will have a plan for dissemination of the intervention by partnering with relevant stakeholders.

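### Power after 30% loss is about 76% on the plan's own figures, not the stated 80%, and the attrition allowance (30% or 20%) and the sample size (96 or 98) are each given two ways

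*Protocol article*

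**What the plan says.** All but one of the figures are in the protocol article under Sample size justification.

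- Error rates: "critical value for type I (α = .05) and type II (β = .2) error". Sidedness is not stated. Allocation is 1:1 and the ICC is 0.5.
- Power before loss: "our total sample size of 98 will provide 89% power to detect a 100 min/week of moderate PA difference between groups". The standardised effect is put at 0.46.
- Expected loss: "Considering an estimated 30% loss to long-term follow-up as reported in similar exercise intervention trials".
- Power after that loss: "our plan to enroll 98 participants should provide adequate power (80%) to detect differences across intervention arms".
- Handling of withdrawals: their data are left out of the analysis, and this is said to have been allowed for in the power analysis, "with an additional 20% added to the target sample size".

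The Data analysis section repeats a loss of up to 30%. The abstract (Methods/design) gives a different total: "we will randomize 96 patients from two regions".

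**The concern.** The same 98 people are credited with 89% power before loss and 80% after losing 30% of them. Power at the smaller number is fixed by the first figure, so the pair can be checked, and it looked too generous. The loss allowance appears as 30% and as an added 20% within a few sentences, and the number to be randomized differs between the abstract and the methods.

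These are the figures from which the team sets its recruitment and retention targets, and by which a reader judges the trial. As written, the team would believe that a 30% loss is tolerable at 80% power.

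**Working it through.** **Inputs.** From Sample size justification: α = 0.05, β = 0.2, effect size d = 0.46 (100 min/week, so an implied SD of 100/0.46 ≈ 217), ICC ρ = 0.5, 1:1 allocation, N = 98, loss 30% or 20%. From the abstract: N = 96. Assumed: a two-sided test, and a variance factor of (1 − ρ), because the formula itself is not in the text.

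**1. Reproduce the 89%.** Non-centrality = d/√(1 − ρ) × √(N/4).
- N = 98: 0.46/0.7071 × 4.950 = 3.220. Power = Φ(3.220 − 1.960) = 89.6% by normal approximation and 89.0% by t-test. The stated figure reproduces.
- Alternatives at N = 98 do not fit: no ICC factor 62%; 1 − ρ² 75%; 1 + ρ 46%; one-sided with (1 − ρ) 94%.

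**2. Power after 30% loss.** Analysed: 0.7 × 98 = 68.6.
- Non-centrality = 2.694. Power = Φ(2.694 − 1.960) = 76.9% normal, 75.6% t.
- With 96 enrolled: 0.7 × 96 = 67.2, giving 76.0% normal and 74.8% t.

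**3. Check that does not need the formula.** With effect and variance fixed, non-centrality scales with √N. A two-sided power of 89% implies 1.960 + 1.227 = 3.187. Multiplying by √0.7 = 0.837 gives 2.666, and Φ(2.666 − 1.960) = 76.0%. Over the rounding of 89% (88.5 to 89.5%) the result is 75.3 to 76.7%. None of these reaches 80%.

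**4. Number needed for 80%.**
- Normal: N = 4 × (1.960 + 0.8416)² × 0.5/0.46² = 74.2, so 75 whole participants.
- t-test: 76.2, so 77 whole participants.
- Enrolment needed at 30% loss: 74.2/0.7 = 106 to 76.2/0.7 = 109.

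**5. Largest loss compatible with 80%.**

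| Basis | N = 98 | N = 96 |
|---|---|---|
| t-test, 76.2 analysed | 1 − 76.2/98 = 22.2% | 1 − 76.2/96 = 20.6% |
| Normal, 75 whole participants | 1 − 75/98 = 23.5% | 1 − 75/96 = 21.9% |

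Rounding the t-test number up to 77 gives 21.4% (21 of 98) and 19.8% (19 of 96).

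**6. The 20% statement.**
- Adding 20% to the number needed gives 74.2 × 1.2 = 89 to 76.2 × 1.2 = 91, against the 106 to 109 that a 30% loss requires.
- If 98 already contains the 20%, the base is 98/1.2 = 81.7, with power 83.6% (normal) or 82.7% (t), which is not the stated 89%.
- If loss is 20%, 0.8 × 98 = 78.4 are analysed and power is 82.1% (normal) or 81.2% (t). The 80% claim then holds.

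**7. 96 against 98.** With no loss, 96 gives 89.0% (normal) or 88.4% (t), so the effect on power is about 0.6 points. 96 makes six full blocks of 16 (Randomization section), and 48 in group 2 fill six classes of 8 (Group-based physical activity program section). 98 does neither exactly.

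**The case against.** The best defence is that this is small. The claim is one of adequate power, the gap is 3 to 4 points, and 96 against 98 hardly matters numerically. That stands, and it limits the weight of the point, but it does not make the figures agree.

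The two attrition figures may also measure different things: loss to long-term follow-up (30%, described in Data analysis as an upper bound) and withdrawals whose data are dropped (20%). At 20% the 80% claim is met. The article does not draw this distinction, and it attaches the 80% to the 30% loss. What stands is that a reviewer cannot say which figure is the mistake, so simply deleting the 20% sentence would presume the answer.

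Third, Data analysis plans an intention-to-treat analysis of everyone randomized, with multiple imputation as a sensitivity analysis if data are missing at random, so 68.6 is not the only conceivable analysed number. The sample size paragraph, however, excludes withdrawals, and its power claim has to be read with that rule.

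Stronger readings are tempting and are not supported:
- **That 98 is ruled out by the blocks and classes.** A last block can stay incomplete and a class size is nominal. The design favours 96 but does not exclude 98.
- **That the planners multiplied by 1.3 instead of dividing by 0.7.** 75 × 1.3 = 97.5 is suggestive, but the article does not show its working.
- **That true power is far lower because the ICC should not shrink the variance.** That is a separate question about the variance assumption. It adds nothing to this inconsistency.

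**Conclusion.** The point holds as an internal contradiction of modest size. On the assumptions that reproduce the plan's 89%, power after 30% loss from 98 is about 76%, not 80%. The scaling check reaches the same answer without the missing formula, and rounding of the effect size (0.455 to 0.465) moves the result only between 75% and 78%. The 30% and 20% allowances cannot both underlie the stated figures, and 96 and 98 are both given as the trial's size in current text.

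All power figures here assume a two-sided 0.05 test and are conditional on the plan's own variance assumption. They do not endorse that assumption. A reader might infer that the trial is seriously underpowered or must enrol more; this point alone does not show that.

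**What to change.** - **Sample size.** Reconcile 96 and 98 and use one number throughout. 96 fits the blocks and classes more neatly, but the choice is the sponsor's.
- **Attrition.** State one figure, or define the two quantities if they differ, and correct the sentence on the added 20% accordingly.
- **Power.** If 30% is kept, restate power after loss as about 75 to 77%. Alternatively, state that 80% holds only if loss is no more than about 21 to 22% by t-test (about 22 to 23% by normal approximation with whole participants), with the limit matched to the chosen sample size.
- **Formula.** Give the formula and the sidedness with these figures, and note that they depend on the assumed variance factor.

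The cost is an edit to the abstract and one paragraph. No extra patients and no change of design are needed.

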#### Data analysis

Principal Investigators (Stanford University and Emory University) will be given access to the cleaned data sets. Project data sets will be housed on the REDCap hosted by the respective universities and all data sets will be password protected. To ensure confidentiality, data dispersed to project team members will be blinded of any identifying participant information.

Between-group differences in primary and secondary outcomes will be assessed at 8 and 16 weeks. We will test for differences in primary and secondary outcomes to assess treatment effects using multivariate regression models adjusting for baseline characteristics. We will use mixed-effects linear and logistic regression models to predict changes in continuous PA levels and probability of achieving PA recommendations by regressing study arm, study centers, and an interaction between study arm*centers. The mixed model will include one random effect term accounting for the correlation within study center. Analysis of effectiveness will be according to an intention-to-treat analysis including all enrolled and randomized persons into our analysis. Irrespective of compliance with treatment, all participants will be encouraged to continue with the scheduled outcome evaluation until the end of the study. However, as high as up to 30% loss to long-term follow-up would be expected. The characteristics for those participants without complete follow-up will be examined. If missing data is determined to be random, we will perform a sensitivity analysis using multiple imputation-based methods. If missing observations cannot be assumed to be random, pattern mixture models will be considered [64].

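### One section discards all data from participants who withdraw, another promises an intention-to-treat analysis of everyone randomised; both cannot be followed

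*Protocol article*

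**What the plan says.** Under Sample size justification the rule is unqualified: "Data gathered from those who withdraw from the study will not be used for statistical analyses". The next sentence treats this as a matter of numbers: "This has been accounted for when completing the power analysis, with an additional 20% added to the target sample size". The same paragraph uses a different attrition figure for power: "Considering an estimated 30% loss to long-term follow-up as reported in similar exercise intervention trials".

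Under Data analysis the population is defined the other way: "Analysis of effectiveness will be according to an intention-to-treat analysis including all enrolled and randomized persons into our analysis". That section also says that, whatever their compliance, "all participants will be encouraged to continue with the scheduled outcome evaluation until the end of the study", and it repeats the larger attrition figure: "However, as high as up to 30% loss to long-term follow-up would be expected".

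On missing data it says "If missing data is determined to be random, we will perform a sensitivity analysis using multiple imputation-based methods" and "If missing observations cannot be assumed to be random, pattern mixture models will be considered".

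The primary outcome (Expected outcome) is the between-group difference in change in weekly minutes of moderate-to-vigorous activity at 16 weeks. Data analysis also plans comparisons at 8 weeks. The article does not separate withdrawal from loss to follow-up.

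**The concern.** An analyst cannot include every randomised person and also use no data from those who withdrew. If the exclusion governs, someone who completes the 8-week visit and then withdraws loses the baseline values, the 8-week values and all weekly wearable data. That person disappears even from the 8-week comparison, where the outcome was observed.

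The comparison is then between those who stayed in each arm. Participants are unblinded once the intervention starts, and only group 2 has twice-weekly classes, so the reasons for leaving, and who leaves, may differ by arm. Adding participants to allow for withdrawal protects precision. It does nothing about this bias.

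The missing-data provisions do not close the gap. Imputation is a sensitivity analysis only, and it would normally draw on the partial data that the exclusion discards. Its use also depends on first determining that data are missing at random. Observed data cannot distinguish that from missing not at random, so the switch between the two methods has no empirical basis.

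**Working it through.** **1. The plan's own power figure.** Inputs from Sample size justification: total N = 98, 1:1 allocation, effect size 0.46 (100 min/week, so SD = 100/0.46 ≈ 217), ICC ρ = 0.5, α = 0.05. Sidedness is not stated; two-sided is assumed. The formula is not visible in the text. The form that reproduces the result multiplies the variance by (1 − ρ):

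power = Φ( 0.46/√(1 − 0.5) × √(n/2) − 1.96 ), with n per arm.

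- n = 49: 0.6505 × 4.950 − 1.96 = 1.260, power 89.6%. This agrees with the stated 89%.
- Without the ICC term, two-sided power is 62.4%, which does not agree. The (1 − ρ) form is therefore used below.

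**2. Power if withdrawers are excluded.**

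- 30% excluded: 98 × 0.70 = 68.6, about 69 analysed (34.3 per arm). 0.6505 × 4.141 − 1.96 = 0.734, power 76.9%. The plan states 80%.
- 20% excluded: 98 × 0.80 = 78.4, about 78 analysed. Power 82.1%.
- 80% power needs 76 analysed: 76/0.70 = 109 enrolled at 30% loss, or 76/0.80 = 95 at 20%.

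The 80% claim therefore holds at 20% loss but not at the 30% to which the plan attaches it.

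**3. Bias of a completer comparison.** Let d be the proportion withdrawing in an arm, and D how much less withdrawers gain than completers (min/week, after any baseline adjustment). In each arm, mean of all randomised = mean of completers − d × D. Hence:

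bias (group 2 minus group 1) = d2·D2 − d1·D1.

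The documents give no D, so these inputs are assumed. Average loss is 30% throughout.

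| Loss, group 1 / group 2 | D1, D2 = 50, 50 | 100, 100 | 50, 100 | 0, 100 |
|---|---|---|---|---|
| 30% / 30% | 0 | 0 | +15 | +30 |
| 25% / 35% | +5 | +10 | +22.5 | +35 |
| 20% / 40% | +10 | +20 | +30 | +40 |
| 35% / 25% | −5 | −10 | +7.5 | +25 |

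The range is −10 to +40 min/week against a target of 100. Most entries are positive because the grid never sets D1 above D2 and mostly gives group 2 the higher or equal loss. Mirrored inputs reverse the sign: with loss of 40% / 20% and D = 100, 0, the bias is 0.20 × 0 − 0.40 × 100 = −40.

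**4. With dropout rates cited in the article.** The Discussion cites a dialysis exercise study with dropout of 23.8% for rehabilitation-centre and 16.7% for home-based exercise. Taking these for groups 2 and 1, with D = 100 in both arms: 0.238 × 100 − 0.167 × 100 = +7.1 min/week.

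**The case against.** The strongest reply is that stopping the classes is not withdrawing from the study. Data analysis encourages outcome evaluation irrespective of compliance, and the primary outcome comes from a wearable given to both arms and synced weekly. A group 2 participant who stops attending can still supply primary data. This stands: it makes differential withdrawal less certain than the twice-weekly classes alone suggest. It does not cover those who do withdraw.

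Second, a reader might infer that 30% of participants will be excluded. The documents do not say so. The 30% is loss to follow-up, the withdrawal rule carries its own 20% allowance, and someone who misses the 16-week visit without withdrawing is not covered by the exclusion. Hence the range of 20–30%.

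Third, a reader might infer that the exclusion favours the class arm, perhaps by a large amount. For example, with no true effect, suppose 60% in each arm gain 100 min/week and the rest gain nothing. If all non-gainers leave group 2 and half leave group 1, completer means are 60/0.6 = 100 and 60/0.8 = 75, a false benefit of 25. Those inputs are extreme. With the cited dropout rates in the same model, the means are 60/0.762 = 78.7 and 60/0.833 = 72.0, a difference of 6.7. Nor is bias absent only when withdrawal is unrelated to outcome or equal across arms: it vanishes whenever d1·D1 = d2·D2, and it can be present with equal loss.

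Fourth, the choice of primary model and the construction of the imputation are details that an article may leave to an analysis plan not shown here. That is fair, and their absence is not the complaint. The complaint is that two stated rules conflict.

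**Conclusion.** The point stands as a contradiction between two explicit rules, which leaves the primary analysis population undefined. It must be resolved before analysis, because one reading compares the groups as randomised and the other does not.

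The bias under the exclusion is a risk of unknown size and direction. The −10 to +40 min/week range and the figure of about +7 both rest on assumed gaps between completers and withdrawers, and the second also borrows dropout rates from a different setting. The documents do not support a claim that the bias must favour group 2.

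The power result is firmer but depends on the inferred formula and a two-sided test: about 77% rather than 80% if 30% are excluded, and 82% if 20% are. That observed data cannot establish whether missingness is random is correct, and is secondary to the contradiction.

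**What to change.** - Delete the exclusion sentence under Sample size justification, or limit it to data for which the participant revokes consent to use.
- State that all data collected up to withdrawal are analysed in the arm randomised.
- Make the primary analysis a repeated-measures mixed model using all observed baseline, 8-week and 16-week values, or multiple imputation on the same data. The model needs a within-participant correlation term; the one described has a single random effect, for centre.
- Run a missing-not-at-random sensitivity analysis, for example a delta-adjusted pattern-mixture model, in every case and not only after a judgement about randomness.
- Distinguish withdrawal from loss to follow-up, choose one attrition figure (20% or 30%) or explain why both are needed, and restate the power after attrition.

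The cost is wording and one additional sensitivity analysis. Resolving the contradiction needs no extra participants or visits. If 80% power is to be kept at 30% loss with losses left out of the analysis, the arithmetic above gives 109 enrolled; otherwise the lower power should be stated.
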